## Methods and analysis

### Setting, patient population and personnel

The study will be carried out in the resuscitation room of the ED of Skåne’s University Hospital at Lund (referred to hereafter as Lund’s RR). Lund’s RR is designed for the simultaneous management of three priority 1 patients. EM access during clinical practice will be provided in September 2023. The study population consists of consecutive priority 1 patients managed in the Lund’s RR during the 6-month period prior to, and the 6-month pilot study period following EM implementation. Patients are deemed to be priority 1 based on vital signs and symptoms according to the Rapid Emergency Triage and Treatment System (http://predicare.se/) the most commonly used triage system in Sweden. The yearly number of priority 1 patients treated in Lund’s RR is roughly 4000 and consists of adult patients (>18 years) with medical or surgical emergencies and patients of all ages with level 1 trauma. Most of these patients are brought to the RR via ambulance, and only occasionally are they identified at the triage or at later stage of ED care. All priority 1 patients are managed immediately in the RR by multidisciplinary resuscitation teams. The core resuscitation team consists of a resident or specialist in emergency medicine, two nurses and one nursing assistant. When the patient is especially critical (for instance, cardiac arrest, level 1 trauma, upper airway obstruction), additional personnel (anaesthesiologists, surgeons, cardiologists, otorhinolaryngologists) supplement the resuscitation team.

### EM: content and format

The EM consists of problem checklists, diagnosis checklists, procedure checklists and fact sheets in digital form. The checklists and fact sheets are accessed through a tablet computer located at each of the three resuscitation sections in the RR and displayed on a large screen visible to all members of the resuscitation team. Problem checklists consist of lists of interventions and diagnoses to consider based on the patient’s presenting symptoms. The popover windows display key clinical features suggestive of specific diagnoses. Diagnosis checklists consist of lists of interventions to consider during the management of a suspected diagnosis. Each intervention is associated with a popover window displaying indications, contraindications or risks associated with the intervention, and details regarding how the intervention is performed, as described in a previous study.^22^ Procedure checklists provide step-by-step guidance for the performance of key procedures as well as pictures. Fact sheets provide information such as medical dosages for sedation and anaesthesia for patients of all ages.

The collection of checklists and fact sheets covers the majority of symptoms, diagnoses and situations that may present in the RR, in accordance with the current European Core Curriculum in Emergency Medicine.^34^ The format and design of each checklist or fact sheet is informed by the literature pertaining to emergency and abnormal checklists in the aviation industry,^35–37^ articles on medical checklists^6 38–40^ and a selection of EMs.^41–44^ The content is customised to local circumstances in Lund’s ED (available medications, medication locations, local routines and phone numbers). EM content and format are further developed through iterative, rapid-cycle simulation-based testing and review by specialists, residents, nurses and nursing assistants who work clinically in Lund’s RR. Internet access to the EM is provided to the ED personnel prior to and during the study to allow for familiarisation and suggestions for improvement. Each checklist and fact sheet is approved by at least one specialist in emergency medicine and one nurse, both of whom work clinically in Lund’s RR.

### EM: protocol for use

EM use during priority 1 management is strongly advocated but not mandatory. The documenting nurse is assigned the specific task of activating the digital EM. Regarding problem and diagnosis checklists, Do-Confirm is the default mode of EM use—the team first manages priority 1 patients without support from the EM. Once the management plan is finalised (a juncture which may be verbally confirmed with the team leader), the documenting nurse then asks the team: “Which checklist should I display?” When a checklist is displayed, the documenting nurse reads aloud each potential intervention or diagnosis for team consideration. The documenting nurse registers on the digital checklist whether each intervention is

Deemed indicated and has already been carried out.Deemed irrelevant or contraindicated.Deemed indicated and will be carried out thanks to EM use.

The physician responsible for patient management has the mandate to request that the EM not be used, to pause or terminate EM use at any time, and to depart from the recommendations featuring on the checklist. Physicians may also request that the EM be displayed directly and used in Read-Do mode or for retrieval of specific information (Sampling mode). Regarding procedure checklists and fact sheets, the default modes of use are Read-Do and Sampling, respectively. After EM use, teams grade the usefulness of the EM on a 1–6 Likert scale prior to logging out. If the documenting nurse logs in to the EM but the EM is not used, the nurse selects among potential reasons for non-use prior to logging out. Teams can also electronically request contact with the investigators to report specific events related to EM use.

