**Methods and analysis:**

This 6-month long study prospectively evaluates a digital EM during management of priority 1 patients in the Skåne University Hospital at Lund’s ED. Resuscitation teams are encouraged to use the EM after a management plan has been derived (‘Do-Confirm’). The documenting nurse activates and reads from the EM, and checklists are displayed on a large screen visible to all team members. Whether the EM is activated, and which sections are displayed, are automatically recorded. Interventions performed thanks to Do-Confirm EM use are registered by the nurse. Fifty cases featuring such interventions are reviewed by specialists in emergency medicine blinded to whether the interventions were performed prior to or after EM use. All interventions are graded as indicated, of neutral relevance or not indicated. The primary outcome measures are the proportions of interventions performed thanks to Do-Confirm EM use graded as indicated, of neutral relevance, and not indicated. A secondary outcome measure is the team’s subjective evaluation of the EM’s value on a Likert scale of 1–6. Team members can report events related to EM use, and information from these events is extracted through structured interviews.

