## Introduction

### Checklists

A checklist is a cognitive aid—consisting of a list of assessments or actions—designed to be carried out systematically. The function of checklists is to improve task performance; checklists are essentially knowledge-translation tools that promote completeness, consistency and alignment with best practice guidelines when carrying out a task.^1^ Checklists work by directing focus, providing facts^2^ and guiding—though not dictating—decision-making. Checklists are also believed to improve performance through other mechanisms, such as reducing mental workload, promoting a shared mental model among team members and empowering team members to voice concerns.^3–5^

There are two basic modes of checklist use.^6^ In Read-Do mode, checklists are used as the task is performed to guide task completion. During the Do-Confirm mode, checklists are used after task performance to verify completeness. Cognitive aids may even be used to retrieve specific information (for instance, the dosage of a specific medication in a specific setting), so-called Sampling mode.^6 7^ Checklists may be used by one or several people, silently or read aloud,^6^ and can be categorised according to the circumstances in which they are used: normal (or routine) situations, emergency situations, and atypical (or non-normal) situations.^6 8^

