### Educational campaign

An educational campaign targeting all personnel who work in Lund’s RR precedes the implementation of the EM in clinical practice. Evidence for the potential benefits of an EM—including results from a locally performed crisis checklist study^22^—is presented, as well as the protocol for EM use. Documenting nurses during priority 1 patient management are taught to log in to the EM, display and navigate between checklists, open popover windows, record whether interventions were not indicated, done before or thanks to checklist access, record the team’s opinion of the EM’s value, request contact with the investigators, and log out. Documenting nurses carry out these functions in addition to their usual documentation tasks.

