### Impact of EM use on resuscitation team performance

The final 50 cases where the EM was used in Do-Confirm mode and interventions were performed thanks to checklist access are identified for external review. The final cases during the 6-month study period are selected to allow personnel the opportunity to integrate the new tool within their clinical practice. The degree to which each intervention is indicated is independently assessed by three specialists in emergency medicine. All three assessors are blinded to whether the intervention was performed before or after EM use. Two assessors are blinded to the content of the EM, while one is involved in the development and use of the EM. Interventions are categorised, based on the available extracted clinical information, as indicated (eg, administering antibiotics to the septic patient), of neutral relevance (eg, measuring liver function tests for the patient with suspected benzodiazepine overdose), or not indicated (ie, overinvestigation or overtreatment, for example, ordering CT to rule out pulmonary embolism for a patient with pulmonary oedema). When the three assessors are not in agreement regarding the degree of indication of the intervention, resolution is reached through discussion, and based on majority opinion if no consensus can be reached. Management is deemed improved when interventions categorised as indicated are carried out thanks to EM use. EM use is deemed to not add value if additional interventions are categorised as of neutral relevance. EM use is deemed detrimental if additional interventions are categorised as not indicated.

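### The bedside form has no entry for an indicated item already planned but not yet done, so planned care is likely to be credited to the emergency manual (EM)

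*Protocol article*

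**What the plan says.** The protocol article, under *EM: protocol for use*, fixes when the checklist is opened: "Once the management plan is finalised (a juncture which may be verbally confirmed with the team leader), the documenting nurse then asks the team" which one to display. The abstract gives the same trigger, a plan that has been derived. The Introduction, under *Checklists*, defines the mode differently: "During the Do-Confirm mode, checklists are used after task performance to verify completeness".

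For each item read aloud the nurse chooses one of three registrations: "Deemed indicated and has already been carried out.Deemed irrelevant or contraindicated.Deemed indicated and will be carried out thanks to EM use". The *Educational campaign* section teaches the same split, asking nurses to "record whether interventions were not indicated, done before or thanks to checklist access". *Data acquisition* stores it as performed before, or thanks to, checklist access.

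Two things depend on the third registration:
- **Case selection.** The final 50 Do-Confirm cases with at least one EM-attributed intervention go to external review (*Impact of EM use on resuscitation team performance*).
- **Primary outcome.** According to the abstract, "The primary outcome measures are the proportions of interventions performed thanks to Do-Confirm EM use graded as indicated, of neutral relevance, and not indicated".

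The primary objective asks whether Do-Confirm use leads to additional interventions.

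**The concern.** A final plan is not a completed plan. When the checklist is opened, an item can be indicated, already decided on, and still pending. Neither of the first two registrations describes it: it has not been carried out, and it is neither irrelevant nor contraindicated. The third fits its timing but credits the EM with a decision the team made unaided.

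If such items are filed under the third registration, the EM is credited with care that is not additional. A case whose only EM-attributed item was already planned would also qualify for review although the EM added nothing. Within the primary outcome, the indicated share shifts towards the rate at which planned items are graded indicated.

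**Working it through.** **1. Can a later step repair the entry?**
- *Assessors.* They grade indication only, and "All three assessors are blinded to whether the intervention was performed before or after EM use". They cannot correct attribution.
- *Chart extraction.* *Data acquisition* lists the interventions performed in the resuscitation room. It does not list whether each was decided before the checklist was displayed. A planned item later carried out looks the same as a prompted one.
- *Training and stored data.* Both repeat the before / thanks-to split.

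The distinction is therefore lost unless it is captured at the bedside.

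**2. The plan's own figure.** *Sample size calculation* gives 75 interventions from 50 patients, a null indicated rate of at most 10%, an alternative of 21%, power of at least 80% and α ≤ 0.05. With X ~ Binomial(75, p), the smallest count r with P(X ≥ r | 0.10) ≤ 0.05 is r = 13:
- P(X ≥ 12 | 0.10) = 0.069, too large
- P(X ≥ 13 | 0.10) = 0.034
- P(X ≥ 13 | 0.21) = 0.82; at 0.20 it is 0.76

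The stated figure reproduces with an exact one-sided test. The cut-off of 13 is derived here; the article does not state it.

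**3. Effect of misfiled items.** Let k of the 75 logged items be already planned, q the indicated rate among those, and p the rate among truly prompted items. Then

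expected indicated share = [(75 − k)p + kq] / 75, and the shift from p is k(q − p)/75.

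The chance of rejecting is P(A + B ≥ 13), with A ~ Binomial(k, q) and B ~ Binomial(75 − k, p) independent. The documents give none of k, q or p, so the values below are assumptions.

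With p = 0.10 (null true; 3.4% at k = 0):

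| k of 75 | q = 0.5 | q = 0.8 | q = 0.9 |
|---|---|---|---|
| 4 | 11% | 20% | 24% |
| 8 | 26% | 58% | 70% |
| 15 | 62% | 98% | 99.8% |

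For example, with k = 8 and q = 0.9 the expected share is (67 × 0.10 + 8 × 0.9)/75 = 13.9/75 = 18.5%.

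**4. Away from the null.** With k = 8 and q = 0.9:

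| prompted rate p | logged share | shift, percentage points |
|---|---|---|
| 50% | (33.5 + 7.2)/75 = 54.3% | +4.3 |
| 70% | (46.9 + 7.2)/75 = 72.1% | +2.1 |
| 80% | (53.6 + 7.2)/75 = 81.1% | +1.1 |
| 90% | (60.3 + 7.2)/75 = 90.0% | 0 |

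If q < p the share falls: with p = 0.95, q = 0.80 and k = 15, it is (57 + 12)/75 = 92%. At p = 0.30 the cut-off of 13 is already passed with probability 99.6% without any misfiling.

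**5. Count.** This part does not depend on q or p. With k = 8, the 75 credited items contain 75 − 8 = 67 that the EM prompted.

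**The case against.** A reader might infer that planned care *is* logged to the EM and that the primary outcome *is* inflated. The document does not support either as a certainty.

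- *Coding.* The third registration has two conditions: the item will be done, and it will be done because of the EM. A planned item fails the second. A careful nurse could choose the first registration, which would place the item correctly before EM use. The coding is undefined, not directed to the EM. This stands, and it limits the claim to likely misfiling.
- *Direction.* The outcome is a set of proportions within EM-attributed items. The indicated share rises only if q > p. The treating team must already have deemed a prompted item indicated, so p well above 10% is plausible. This stands: the large error rates arise only near the null.
- *Frequency.* The team first manages the patient without the EM, so many items may be done by the time of reading. No share is given. This stands.
- *Role of the test.* The null appears only in the sample size section, and *Data analysis* reports the reviewed cases descriptively. The rejection probabilities therefore gauge sensitivity and do not describe a declared decision rule.
- *After versus thanks to.* A reader might also infer that the plan treats everything done after EM use as caused by it. It does not. The training text says thanks to, and before/after appears only in describing what assessors are blinded to.
- *Article scope.* A condensed article may leave coding detail to the full protocol. This carries less weight here, because the article sets out the form, the training and the stored variable, and all three use the same split. An analysis plan could not restore information that was never recorded.

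**Conclusion.** The concern holds as a gap in the stated instrument. The trigger allows items that are planned but pending, no registration describes them, and the nearest one credits the EM. Misfiling is likely but not certain.

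Where it occurs, the number of interventions credited to the EM is overstated, the pool of qualifying cases can only grow, and the word additional in the primary objective loses its force. Those consequences need no assumption about indication rates.

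The effect on the indicated proportion is conditional. It is upward if planned items are indicated more often than prompted ones, absent if the rates are equal, and downward otherwise. For 8 misfiled items of 75, it ranges from a false rejection chance of 26% to 70% at the 10% null (planned items 50% to 90% indicated) to a rise of at most about 4 percentage points once prompted items reach 50% (planned items up to 90% indicated). The share of misfiled items and both indication rates are assumptions.

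**What to change.** 1. Add a fourth registration to the digital checklist: *Deemed indicated, already planned before the checklist was displayed, not yet carried out*.
2. Exclude these items from the EM-attributed set, both for selecting the 50 cases and for the primary outcome. Only items neither done nor planned beforehand count as EM-prompted.
3. Teach the distinction in the educational campaign.
4. Reconcile the Introduction's account of Do-Confirm (after task performance) with the trigger in *EM: protocol for use* (plan finalised).

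The cost is one more button and one line of training. Qualifying cases may accrue more slowly, because cases whose only credited items were already planned drop out. The change must be in place before data collection, since the information cannot be reconstructed later.

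### The registration scheme has no entry for interventions already planned but still pending, so such items can be credited to the EM and may bias the primary outcome

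*Protocol article*

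**What the plan says.** All references are to the protocol article.

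- **When the EM is opened.** *EM: protocol for use* sets the moment: "Once the management plan is finalised (a juncture which may be verbally confirmed with the team leader"). The abstract agrees: "Resuscitation teams are encouraged to use the EM after a management plan has been derived". The *Checklists* section of the Introduction defines the mode differently: "During the Do-Confirm mode, checklists are used after task performance to verify completeness".
- **What the nurse can record.** *EM: protocol for use* lists three entries per intervention: "Deemed indicated and has already been carried out", "Deemed irrelevant or contraindicated" and "Deemed indicated and will be carried out thanks to EM use". *Educational campaign* trains nurses on the same split, namely to "record whether interventions were not indicated, done before or thanks to checklist access". *Data acquisition* again separates only interventions performed before checklist access from those performed because of it.
- **What the entry feeds.** In *Impact of EM use on resuscitation team performance*, the attributed entries decide which final 50 cases go to external review. In the abstract they are the denominator of the primary outcome. The conclusion drawn from them is causal: "Management is deemed improved when interventions categorised as indicated are carried out thanks to EM use".

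**The concern.** If the EM were opened only after all planned care had been delivered, the three entries would cover every case. Under the trigger actually set, some planned care will often still be outstanding, for example a scan requested or a drug being prepared. The team has already decided on that item, so it was not prompted by the EM. It has not been done, so the first entry is false. It is neither irrelevant nor contraindicated, so the second is false too. The third is true as to indication and future performance, and false only as to cause.

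Two things are at stake. One is the count of interventions and cases attributed to the EM. The other is the proportion of attributed interventions graded indicated. No later step described in the article would correct a wrong attribution. The assessors grade whether an intervention was indicated, not what prompted it, and they are blinded to whether it came before or after EM use. The chart extraction lists interventions performed in the resuscitation room (RR), not what the team intended before the EM was opened. Prior intent that is not captured at the bedside cannot be reliably recovered.

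**Working it through.** **Inputs from the protocol** (*Sample size calculation*): 50 patients, 75 attributed interventions, null indicated rate at most 10%, alternative 21%, power at least 80%, α ≤ 0.05. The sidedness is not stated; the form of the null implies one-sided.

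**Inputs assumed, not in the protocol:** m, the share of attributed entries that are really planned care (5% to 30%); q, the rate at which planned care is graded indicated (80% to 100%, with 50% as a milder case); p, the true indicated rate among genuinely prompted items.

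**Step 1: the plan's own figure.** With an exact binomial test and n = 75, the smallest count c with P(X ≥ c | 0.10) ≤ 0.05 is 13.
- Actual α = P(X ≥ 13 | 0.10) = 0.034.
- Power = P(X ≥ 13 | 0.21) = 0.821.

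The stated power is reproduced. It treats every attributed entry as truly prompted by the EM.

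**Step 2: effect on the count.** Of 75 attributed entries, 75 × m are planned care. At m = 10% that is 7.5, leaving 67.5; at m = 20% it is 15, leaving 60. This happens whatever the grading. A case whose only attributed entry is planned care would also qualify for review wrongly.

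**Step 3: effect on the proportion.** Misfiled items enter numerator and denominator alike:

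observed rate = (1 − m)p + mq, so shift = m(q − p).

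The shift is zero when q = p, upward when q > p and downward when q < p.

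**Step 4: numbers when p is at the null, 10%.** Rejection probability is P(X ≥ 13 | n = 75, observed rate).

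| m | q | Observed rate | P(reject) |
|---|---|---|---|
| 0 | – | 10% | 0.034 |
| 5% | 90% | 14% | 0.25 |
| 10% | 90% | 0.90 × 10% + 0.10 × 90% = 18% | 0.61 |
| 15% | 90% | 22% | 0.87 |
| 20% | 90% | 26% | 0.97 |
| 10% | 50% | 14% | 0.25 |
| 15% | 50% | 16% | 0.42 |
| 20% | 50% | 18% | 0.61 |

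Over m = 5% to 30% and q = 80% to 100%, the observed rate runs from 13.5% to 37.0% and the rejection probability from 0.21 to about 1.00.

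**Step 5: numbers when p is well above the null** (m = 10%, q = 90%).
- p = 50%: 0.90 × 50% + 0.10 × 90% = 54%.
- p = 80%: 0.90 × 80% + 0.10 × 90% = 81%.

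The test's verdict would not change here. Already at p = 30% with no misfiling, P(X ≥ 13) = 0.996.

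**The case against.** A reader might infer that planned care *is* logged as prompted by the EM and that the primary outcome is therefore inflated. The protocol does not support that. The third entry carries a causal condition, and a nurse who applies it strictly would not use it for something already decided. The nurse could equally record an ordered test as already done, which would leave the attributed set untouched. The direction of bias is not fixed either. Every item under the third entry has been judged indicated by the team, so a 10% against 90% split in external grading is an extreme assumption. If planned and prompted items are graded alike, the proportion does not move.

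Three further points can be made for the plan. The Introduction's definition of Do-Confirm would leave little care pending. The third entry records an intention, but the article already extracts the interventions performed for the reviewed cases, so items never carried out can be identified. And *Data analysis* reports the graded proportions descriptively; the test against 10% appears only in the sample size section and the legend of Figure 2.

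These points limit the size and the certainty of the bias, and they stand to that extent. They do not supply an entry for pending care. The operative trigger is a finished plan, the training text repeats the same split, and a strict reading of the third entry leaves the nurse with no true option. Entry instructions could sit in a fuller protocol, but the categories themselves are set out here and do not match the trigger set beside them.

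**Conclusion.** The gap is in the text: the stated trigger makes planned but pending care likely, and none of the three entries describes it. Such items must be misfiled, and some can be credited to the EM. If they are, the count of attributed interventions and qualifying cases is too high. The indicated proportion is also too high if planned care is graded indicated more often than prompted care, which is plausible because the team chose it unaided, but is not stated.

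The size is unknown. It rests on m, q and p, none of which the protocol gives. The effect on the proportion is large only if the true rate is near the 10% null (10% read as 18%, with rejection 0.61 against 0.034, at m = 10% and q = 90%). It is small if most prompted items are truly indicated (50% to 54%, 80% to 81%). The wrong causal credit to the EM remains in either case. This is worth correcting before launch because the information cannot be recovered later and the repair is cheap; it does not show that the primary result will be wrong.

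**What to change.** 1. Before launch, add a fourth entry to the digital checklist: *indicated, already in the plan before the EM was opened, not yet carried out*. Exclude it from the set attributed to the EM, both for selecting the 50 cases and for the primary outcome. Add one line on it to the nurse training.
2. Reconcile the timing of Do-Confirm use between the *Checklists* section and *EM: protocol for use*, so that the trigger and the entries fit together.
3. For the reviewed cases, check third-entry items against the interventions already listed in the chart extraction under *Data acquisition*. Report separately those not found as performed, allowing for items carried out after the patient left the RR.

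The cost is one button, one line of training and a check on data already collected. The downside is slightly more registration work for the documenting nurse and fewer countable interventions. The change concerns data recording only.
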